### Immunosuppression

All patients receive induction therapy with basiliximab dosed at 20 mg intravenously on the day of transplantation and on day 4 post transplantation, as per label recommendations. Patients are randomised to receive everolimus at an initial dose of 1.5 mg/day with a reduced dose of cyclosporine and 3 mg/day with tacrolimus within the first 24 h post transplantation. Thereafter, the dose of everolimus is adjusted to the target trough concentration of 3–8 ng/mL throughout the study period. Treatment with CNI, tacrolimus, or cyclosporine, is initiated within the first 24 h post transplantation, and the dose of CNI is adjusted to maintain the target trough levels, as shown in Fig. 1. In the control group, patients receive mycophenolic acid at a dose of 1.44 g/day enteric-coated mycophenolate sodium or at a dose of 2 g/day mycophenolate mofetil with a standard dose of tacrolimus. Dose adjustments and interruptions are allowed for tolerability reasons as defined in the protocol and are recorded. All patients receive corticosteroids at a minimum dose of 5 mg/day prednisolone or equivalent until month 12. Acute rejections are treated according to local practice and physicians’ discretion. All patients who prematurely withdraw from the study are provided with follow-up medical care/referred for appropriate ongoing care, as per the local practice.

### Concomitant medication

Mandatory CMV prophylactic therapy with valganciclovir is recommended for at least 3 months in the case of high- to moderate-risk patients (CMV-positive donor/CMV-negative recipients or CMV-positive donor/CMV-positive recipients). All patients receive prophylactic treatment for *Pneumocystis jirovecii* pneumonia with trimethoprim/sulfamethoxazole for a period of 6 months. All medications and significant non-drug therapies administered after the initiation of the study drug are recorded.

### Data collection

Patient visits are scheduled at baseline, and at months 1, 3, 6, 9, and 12 post transplantation. A detailed list of all study assessments and visits is shown in Table 4. Patients who discontinue the study drug and those who prematurely withdraw from the study are scheduled for a visit and all the assessments listed for visit 6 are performed.

**Table 4 Tab4:** Assessment schedule

	12-month study period						
Month	Baseline	1	3	6	9	Premature end of treatment/withdrawal	12
Visit	1	2	3	4	5	6	7
Enrolment							
Informed consent	X						
Inclusion/Exclusion	X						
Randomisation	X						
Demography	X						
General medical history	X						
Transplantation information	X						
Viral serology	X						
Pregnancy test (β-HCG)	X						
Interventions							
Trough levels (everolimus, cyclosporine, tacrolimus)		X	X	X	X	X	X
Assessments							
Physical examination	X					X	X
Vital signs	X	X	X	X	X	X	X
Study medication check		X	X	X	X	X	X
Haematology/Biochemistry	X	X	X	X	X	X	X
Urinalysis		X	X	X	X	X	X
Viral assessments		X	X	X	X	X	X
Serum for non-HLA antibodies and DSA	X			X		X	X
Echocardiography (LVH)	X					X	X
Protocol renal allograft biopsy^a^	X			X			X
Biomarker assessments^b^	X	X				X	X
CMV substudy^b^	X					X	X
Wound healing complications	As necessary						
Rejection episodes							
Indicated renal allograft biopsy							
Dialysis							
AEs/SAEs/Infections/Comments							
Concomitant therapy							
Immunosuppressive therapy							
End of treatment						X	X
End of study						X	X

*β-HCG* human chorionic gonadotropin, *AE* adverse events, *DSA* donor-specific antibodies, *HLA* human leukocyte antigen, *LVH* left ventricular hypertrophy, *SAE* severe adverse events

^a^Not mandatory. Can be performed according to centre practice

^b^Only in selected centres and patients

#### Renal function

Renal function is assessed by determining the glomerular filtrate rate using serum creatinine values according to the Nankivell formula [42] and used as the primary outcome measure in the study. In addition, as a secondary efficacy variable, the glomerular filtration rate is calculated using the Cockcroft-Gault method [43], the modification of diet in renal disease (MDRD) method [44–46], and the Chronic Kidney Disease Epidemiology Collaboration (CKD-EPI) method [47]. Serum creatinine levels are analysed using venous blood drawn and analysed in the local laboratory.

#### Outcome measures

BPAR is defined as rejections that are acute and proven by biopsy. The time to BPAR is the time from randomisation to the date of first documented BPAR. Graft loss is defined as a failure to discontinue dialysis or if the patient undergoes graft nephrectomy. Overall survival is defined as time from date of randomisation to death due to any cause. Delayed graft function is defined as the need for dialysis within the first 7 days post transplantation excluding the first day, and the duration is defined from the first dialysis day up to the last. Slow graft function is defined as serum creatinine >3.0 mg/dL at day 5.

#### Kidney allograft biopsy

Optional allograft biopsies are performed intra-operatively at the time of transplantation and at month 12. A control biopsy at month 6 may be performed according to centre practice. In all cases of suspected acute rejection, a graft biopsy is performed prior to, or within 24 h of initiation of anti-rejection therapy. All biopsies are read by the local pathologist according to the updated Banff 2009 criteria. Optional biopsies are assessed for the presence of interstitial fibrosis and tubular atrophy using the Banff 2007 criteria.

#### Non-HLA and HLA antibodies

The presence and evolution of non-HLA and HLA antibodies, and among those especially DSA antibodies in the serum, is evaluated at a central laboratory. Blood samples (5 mL) are collected for all patients at baseline, month 6, and month 12.

#### LVH and diastolic dysfunction

The echocardiographic analysis included assessments of the end-diastolic interventricular septum, LV end-diastolic posterior wall thickness, LV end-diastolic diameter, LV end-systolic diameter, LV end-diastolic volume, LV end-systolic volume, LV ejection fraction, relative wall thickness, and LV mass also expressed as LV mass index [48]. LVH was defined as an LV mass index exceeding 110 g/m^2^ in women and 125 g/m^2^ in men, and a value of 0.44 was taken as cut-off point for abnormal relative wall thickness [49]. Diastolic dysfunction was assessed and graded according to the guidelines of the American Society of Echocardiography [50].

#### CMV substudy

In this optional substudy, 4.7 mL of whole blood is drawn into a lithium heparin-containing tube at baseline and at month 12 or at the end of study/treatment, and shipped on the same day to a central laboratory at 4 °C. This substudy prospectively monitors the incidence of viraemia by analysis of viral load, CMV-specific T-cell frequency, phenotype and functionality, and regulatory T-cells, and T- and NK-cell subsets.

#### Data Monitoring Board

An external and independent Data Safety Monitoring Board was instituted before the start of the study. The board reviews safety-related issues on an ongoing basis and is entitled to make recommendations for changes in study conduct.

### Statistical analysis

The primary efficacy variable, i.e., renal function at month 12 after randomisation between the treatment groups will be compared with the analysis of covariance (ANCOVA) model, using the treatment and centre as factors, and the estimated glomerular filtration rate at baseline as a covariate. Missing estimated glomerular filtration values will be handled within the ANCOVA analysis by multiple imputations by the last available post-baseline observation carried forward (LOCF) approach. Assuming a common dropout rate of 20 %, a sample size of 612 patients (204 patients in each treatment arm) is required in the study, so as to have at least 80 % power to demonstrate non-inferiority (2.5 % margin, one-sided *t* test) for the primary endpoint.

The primary analysis is based on the full analysis set that consists of all patients who receive at least one dose of the study drug. The per-protocol set includes all patients in the full analysis set who do not have any major deviations from the protocol procedures that may impact the study outcomes. The safety set consists of all patients who receive at least one dose of the study drug and had at least one post-baseline safety assessment.

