CENTRAL (ASE01) Mjörnstedt et al. [32]	*N* = 204 de novo patients Initial treatment with CsA + EC-MPS + steroids + basiliximab induction followed by randomisation at 7 weeks post transplant to either continue the same regimen, or convert to EVR (C0 6–10 ng/mL) + EC-MPS	36-month, open-label, parallel-group study	• From week 7 to month 12, change in mGFR was significantly greater with EVR vs. the CsA arm (4.9 vs. 0.0 mL/min; *p* = 0.012; ANCOVA). • No differences in graft or patient survival for both the groups • The 12-month incidence of BPAR was significantly high in the EVR arm vs. the CsA arm (27.5 % vs. 11.0 %; *p* = 0.004)

*ANCOVA* analysis of covariance, *BPAR* biopsy-proven acute rejection, *C0* trough levels, *C2* two hours post-dose, *cGFR* calculated glomerular filtration rate, *CMV* cytomegalovirus, *CNI* calcineurin inhibitors, *CrCl* creatinine clearance, *CsA* cyclosporine, *DGF* delayed graft function, *EC-MPS* enteric-coated mycophenolate sodium, *eGFR* glomerular filtration rate, *EVR* everolimus, *IL* interleukin, *MDRD* modification of diet in renal disease, *mGFR* measured glomerular filtration rate, *MMF* mycophenolate mofetil, *MPA* mycophenolic acid, *NODM* new-onset diabetes mellitus, *NS* not significant, *vs.* versus

The ATHENA trial is designed to further increase our knowledge and seek answers relating to the use of everolimus in CNI minimisation protocols in *de novo* kidney transplant patients. The ATHENA study assesses the change in renal function at 12 months post transplant as the primary objective. The design of the trial is described here.

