## Methods/Design

### Study design

ATHENA (Clinicaltrials.gov: NCT01843348; EUDRACT number: 2011-005238-21) is a 12-month, multicentre, randomised, international, prospective, controlled, open-label study with three parallel treatment groups in de novo kidney transplant recipients receiving renal allografts from deceased or living donors (protocol version 3, 29 July 2014). Eligible patients are randomised before transplantation using a validated system to ensure an unbiased treatment assignment in a 1:1:1 ratio to receive either everolimus with a reduced dose of cyclosporine, or everolimus with tacrolimus, or a standard regimen of mycophenolic acid with tacrolimus (Fig. 1). All patients receive induction therapy with basiliximab and maintenance steroids. At the time of randomisation, patients are stratified based on the donor type (living donor, deceased standard criteria donor, or deceased expanded criteria donor) and the participation of the recipient in the European Senior Program. The study protocol and the proposed informed consent form were reviewed and approved by the national institutional review boards or independent ethics committees at each centre and the federal institute for drugs and medical devices (Additional file 1). Written informed consent was obtained from all patients. The clinical study was designed and is conducted in accordance with the ethical principles laid down in the Declaration of Helsinki.

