### Study population

The study population comprises de novo adult patients receiving a primary or secondary kidney transplant from a deceased or living donor. In the case of second kidney transplants, patients could be enrolled only if the first graft loss is due to non-immunological reasons. Patients are not eligible for the study if they are recipients of an ABO-incompatible transplants, have pre-existing donor-specific antibodies (DSA), or have an organ cold ischemia time longer than 30 h. Patients with pre-existing human leukocyte antigen (HLA)-antibodies not directed against the donor and less than 20 % panel reactivity at the time of transplant were included in the study. Detailed inclusion and exclusion criteria are shown in Table 2.

**Table 2 Tab2:** Key inclusion and exclusion criteria

Key inclusion criteria	
•	Male or female renal allograft recipients aged18 years or older
•	Recipients of a primary or secondary kidney transplant from a deceased or living unrelated/related donor
•	Written informed consent to participate in the study
•	Cold ischemia time below 30 hours
•	Female patients who are menstruating and capable of conceiving must test negative for pregnancy before study enrolment and during the conduct of the study
Key exclusion criteria	
•	Multi-organ transplant recipients
•	Graft loss due to immunological reasons in the first year after transplantation (in case of secondary transplantation)
•	ABO-incompatible transplants
•	A current panel reactive antibody level of >20 % (within 4 months before enrolment) or positive Luminex test for any donor antigen
•	Existing antibodies against the HLA-type of the receiving transplant (known to the investigator at the time of transplantation)
•	History of malignancy during the last 5 years, except squamous or basal cell carcinoma of the skin, renal cell carcinoma ≤ T1N0M0, prostate adenocarcinoma ≤ T1N0M0, and adenocarcinoma of the thyroid
•	Thrombocytopenia or leukopenia, uncontrolled hypercholesterolemia, or hypertriglyceridemia
•	Pregnant or nursing (lactating) women Women of child-bearing age, unless they are using effective methods of contraception

*HLA* human leukocyte antigen

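### The primary ANCOVA adjusts for a pre-transplant eGFR that probably says little about the graft, and omits the stratification factors that could add precision

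*Protocol article*

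**What the plan says.** - **Model.** The Statistical analysis section compares renal function at month 12 by ANCOVA, with factors for treatment and centre and with "the estimated glomerular filtration rate at baseline as a covariate".
- **Randomisation.** Under Study design: "Eligible patients are randomised before transplantation using a validated system". The same section lists the stratification factors: donor type in three classes (living, deceased standard criteria, deceased expanded criteria) and participation in the European Senior Program. Neither appears among the model terms.
- **Schedule.** Under Data collection: "Patient visits are scheduled at baseline, and at months 1, 3, 6, 9, and 12 post transplantation". Table 4 ticks consent, eligibility, randomisation and haematology/biochemistry together at visit 1 (Baseline). The next tick for biochemistry is visit 2, at month 1.
- **Measurement.** Under Renal function: "Renal function is assessed by determining the glomerular filtrate rate using serum creatinine values according to the Nankivell formula".
- **Population.** Under Study population: "de novo adult patients receiving a primary or secondary kidney transplant from a deceased or living donor".
- **Treatment start.** The Immunosuppression section starts everolimus and the calcineurin inhibitor in the first day after surgery.

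**The concern.** In most trials with a continuous endpoint, the baseline value of that endpoint is the best covariate, because it is an earlier reading of the same quantity. Here it is not. The month-12 value measures the transplanted organ. The baseline value, on the article's own schedule, measures what the patient had before that organ was in place: native kidneys or, in a second transplant, also the failed first graft. There is little reason to expect the two to be closely related.

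What is at stake is efficiency in the primary non-inferiority comparison. The model uses its one continuous covariate on a quantity that probably explains little. It leaves out two factors that are known before randomisation, describe the graft or the recipient, and were thought important enough to stratify on. If those factors are prognostic, stratification has already balanced them across arms. Omitting them from the model then leaves their variance in the residual, and the confidence interval is wider than it needs to be.

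**Working it through.** **1. When is baseline eGFR measured?**

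| Element | Where | Timing |
|---|---|---|
| Randomisation | Study design | before transplantation |
| Randomisation and biochemistry | Table 4, visit 1 | same visit |
| Next scheduled biochemistry | Table 4, visit 2 | month 1 |
| Values used for carrying forward | Statistical analysis | called post-baseline, so distinct from baseline |

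No other eGFR baseline is defined, so the covariate is a pre-transplant value. One limit applies: the article does not date the sample. Table 4's Baseline column also holds transplantation information and an optional biopsy that the biopsy section places during the operation. The visit may therefore reach the day of surgery. A sample from that day would still not measure established graft function.

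**2. The plan's own figure.** The plan gives 612 patients (204 per arm), 20 % dropout, at least 80 % power and a one-sided t test. It gives no SD and no margin in mL/min, so the number cannot be reproduced from stated inputs. The dropout step is coherent:

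- 204 × 0.8 = 163.2, so 163 evaluable per arm
- 163 / (1 − 0.20) = 203.75, rounded up to 204

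Taking the printed 2.5 % as the one-sided significance level (an assumption) and a true difference of 0, the implied ratio is

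margin/SD = √(2/163) × (1.960 + 0.842) = 0.310.

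**3. What a covariate adds.** A covariate, or set of covariates, with correlation ρ with month-12 eGFR shrinks the residual SD by √(1 − ρ²). At 163 per arm:

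- power = Φ(2.802 / √(1 − ρ²) − 1.960)
- patients needed per arm for 80 % = 163 × (1 − ρ²), rounded up

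| ρ | SD factor | Power at 163 per arm | Per arm for 80 % |
|---|---|---|---|
| 0 | 1.000 | 80.0 % | 163 |
| 0.1 | 0.995 | 80.4 % | 162 |
| 0.2 | 0.980 | 81.6 % | 157 |
| 0.3 | 0.954 | 83.6 % | 149 |
| 0.4 | 0.917 | 86.4 % | 137 |
| 0.5 | 0.866 | 89.9 % | 123 |

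The table needs neither the margin nor the SD, only their ratio.

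**4. Sensitivity to the significance level.** With two everolimus arms a one-sided level of 0.0125 is conceivable. The implied margin/SD is then √(2/163) × (2.241 + 0.842) = 0.342, and power is Φ(3.083 / √(1 − ρ²) − 2.241). This gives 83.9 % at ρ = 0.3 and 90.6 % at ρ = 0.5, so the picture is unchanged.

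**The case against.** The strongest reply is that nothing is broken. A covariate measured before randomisation is independent of arm. Adjusting for it neither biases the comparison nor inflates type I error, and it costs one degree of freedom. Nor is planned power lost: the sample size is described for a t test and claims no gain from adjustment, so at ρ = 0 power stays at 80 %. All of this stands. It limits the point to an efficiency gain not taken.

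It is also fair that the exact date of the baseline sample is something a condensed article may leave to the full protocol, and that the correlations in the table are not in the article. The illustration is labelled accordingly.

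Two stronger readings are tempting, and the article supports neither.

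- **Bias towards non-inferiority.** A reader might infer that an early post-transplant creatinine will serve as baseline. Such values exist, since slow graft function is judged at day 5. That value would be post-randomisation and open to the effect of the study drugs, so adjusting for it could remove part of the treatment effect. But Table 4 makes baseline visit 1 and month 1 visit 2, and the Statistical analysis section separates baseline from post-baseline values. Any size in mL/min would need a correlation, an early effect and an SD that the article does not give. The direction would depend on the sign of the early effect, and the Background argues that lower calcineurin inhibitor exposure can improve renal function.
- **A meaningless change endpoint.** The Background says that the study "assesses the change in renal function at 12 months post transplant as the primary objective". A reader might infer an endpoint of change from a pre-transplant value. The abstract, Study objectives, Table 3 and Statistical analysis all give the level at month 12, so this is one loose sentence.

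**Conclusion.** The point holds as a free improvement. On the article's schedule the baseline covariate is a pre-transplant eGFR that probably predicts little of month-12 graft function, while donor type and European Senior Program participation are missing from the stated primary model. The analysis as written remains valid.

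The gain forgone is between nothing and about 10 points of power. If the added covariates reach a combined correlation of 0.3 to 0.5 with month-12 eGFR, power rises from about 80 % to about 84 to 90 %. This rests on four assumptions: 163 evaluable per arm give 80 % power unadjusted; the 2.5 % is the one-sided level; the true difference is 0; and the correlation is what the factors add beyond terms already in the model. The article gives no figure for how well the two factors, or pre-transplant eGFR, predict the outcome. The case for including the factors does not depend on a particular value, because doing so also makes the model match the randomisation.

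**What to change.** 1. Add donor type (three classes) and European Senior Program participation to the primary ANCOVA, in place of or in addition to pre-transplant eGFR.
2. State when the baseline creatinine is taken, and that no post-transplant eGFR serves as the baseline covariate, because study drugs start within a day of transplantation.
3. If the Background sentence on change is carried into other documents, align it with the month-12 level used elsewhere.

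**Cost.** No new data or visits are needed, since both factors are recorded at randomisation. As main effects they use at most three degrees of freedom (two plus one), negligible against about 3 × 163 = 489 evaluable patients. Because the model is stated in the protocol article, the change may need a protocol clarification as well as analysis-plan wording. It should be made before treatment comparisons are seen; the article reports the trial as still recruiting.

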APOLLO (DE02) Budde et al. [24] Budde et al. [25]	*N* = 93 maintenance patients (≥6 months post transplant) EVR (C0 6–10 ng/mL) + EC-MPS ± steroids vs. standard CNI (CsA C0 80–150 ng/mL or tacrolimus C0 5–10 ng/mL) + EC-MPS ± steroids	12-month, open-label, prospective, multicentre study with follow-up at month 60	• Mean time post transplant was 83.5 months with EVR vs. 70.1 months with CNI • Adjusted mean eGFR values (Nankivell, mL/min/1.73 m^2^) were numerically higher with EVR vs. CNI at month 12 (61.6 vs. 58.8; *p* = NS) and at month 60 (63.0 vs. 57.9; *p* = NS) • Using the MDRD formula, adjusted eGFR at month 12 was significantly higher (+4.9 mL/min/1.73 m^2^) with EVR vs. CNI (*p* = 0.030) • At month 60, for patients who remained on the study drug, mean eGFR was significantly higher with EVR vs. CNI (71.6 vs. 60.6; *p* = 0.005)
EVEREST (IT02) Salvadori et al. [26] Ponticelli et al. [27]	*N* = 285 de novo patients Standard EVR (C0 3–8 ng/mL) with low CsA (C2 350–500 ng/mL) vs. high EVR (C0 8–12 ng/mL) with very low CsA (C2 150–300 ng/mL)	6-month, multicentre, randomised, open-label, parallel-group study with follow-up at 12 months and an extension to 24 months	• Death-censored graft survival was significantly lower with standard EVR vs. the high EVR arm at month 6 (90.2 % vs. 97.9 %, *p* = 0.007) and at month 24 (87.4 % vs. 94.4 %, *p* = 0.048) • No significant difference between groups at months 6 and 24 for mean serum creatinine levels and incidence of BPAR
A1202 Takahashi et al. [28]	*N* = 122 de novo patients EVR (C0 3 to 8 ng/mL) + reduced-dose CsA vs. MMF (2 g/day) + standard-dose CsA. All patients receive basiliximab and steroids	12-month, phase III, multicentre, randomised, open-label, parallel-group, non-inferiority study	• 52 % reduction in CsA exposure was achieved in the EVR group at month 12 • At month 12, EVR with reduced CsA exposure was non-inferior to the MMF group for composite efficacy failure (11.5 % vs. 11.5 %) • Median eGFR at month 12 was comparable between the EVR arm vs. the MMF arm (58.00 vs. 55.25 mL/min/1.73 m^2^; *p* = 0.063)

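### Last-value-carried-forward is applied to the primary eGFR with no exception for graft loss, so excess graft loss in an everolimus arm can be under-penalised in the non-inferiority test

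*Protocol article*

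**What the plan says.** The primary variable is Nankivell eGFR at month 12, compared by ANCOVA "using the treatment and centre as factors, and the estimated glomerular filtration rate at baseline as a covariate". The Statistical analysis section names multiple imputation for missing values, and as the means of doing it the "last available post-baseline observation carried forward (LOCF") approach. That is one rule for all missing values, with no separate provision for graft loss or death.

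The primary population is the "full analysis set that consists of all patients who receive at least one dose of the study drug". No post-baseline eGFR is required for membership.

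Under Outcome measures, "Graft loss is defined as a failure to discontinue dialysis or if the patient undergoes graft nephrectomy". No eGFR value is attached to that event. Graft loss counts in the key secondary composite and as an individual component (Study objectives and Table 3).

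Under Data collection, "Patient visits are scheduled at baseline, and at months 1, 3, 6, 9, and 12 post transplantation". Patients who stop study drug or withdraw are also given the visit 6 assessments, which include biochemistry (Table 4).

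**The concern.** A lost graft is not a missing value in the usual sense: its function is known to have ended. Under the stated rule the month-12 entry is whatever was last recorded, which may be a reading from a working kidney.

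The rule also cannot produce a value for a dosed patient who has no post-baseline creatinine. Grafts that never work are the most likely source of such patients, because randomisation precedes transplantation and study drug starts within 24 hours of it.

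The wording names two different techniques, multiple imputation and LOCF. The problem remains whichever is meant: multiple imputation under missing-at-random would also give a lost graft a value typical of working ones.

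In a non-inferiority test of renal function, anything that softens the worst renal outcome in the arm with more of it moves the result towards success. At stake is whether a non-inferiority claim could stand while one arm loses more kidneys.

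**Working it through.** **1. The plan's own figure.** The dropout step reproduces: 163 / (1 − 0.20) = 203.75, rounded up to 204 per arm, and 3 × 204 = 612. The rest cannot be reproduced. No SD is stated, and the article gives only "2.5 % margin, one-sided", which is not on the mL/min scale.

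**2. Implied margin.** Assume one-sided alpha 0.025, 80 % power and 163 evaluable per arm.

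margin / SD = (1.960 + 0.842) × √(2/163) = 0.310

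This gives 4.7, 6.2 and 7.8 mL/min for assumed SDs of 15, 20 and 25.

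**3. Effect of the rule on the mean difference.** Let d be the excess proportion of graft loss on everolimus, L the carried eGFR and F the mean of working grafts.

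- Loss carried forward: shift = d × (L − F)
- Loss scored 0: shift = d × (0 − F)
- Loss left out: shift = 0
- Masking by LOCF relative to 0: d × L

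With d = 0.05, F = 55 and L = 30 (all assumed), the shift is −1.25 mL/min under LOCF and −2.75 when loss is scored 0. The arm is still penalised, but less.

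**4. Range of the masking d × L, for L = 20 to 50.**

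| Excess loss (assumed) | Masking, mL/min | Share of the 6.2 margin (SD 20) |
|---|---|---|
| 2 points | 0.4 to 1.0 | 6 to 16 % |
| 5 points | 1.0 to 2.5 | 16 to 40 % |

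At 5 points the share is 1.0/4.65 to 2.5/4.65 = 22 to 54 % for SD 15, and 1.0/7.76 to 2.5/7.76 = 13 to 32 % for SD 25.

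**5. Effect on the decision (illustration).** This is a simulation of an unadjusted two-arm comparison with 204 per arm and 4000 runs. It assumes SD 20, margin 6.2, working-graft mean 55 in both arms and control graft loss 4 %. The carried value is about 35, 40 % of losses have no post-baseline value, and there is no other dropout. Cells show the chance of declaring non-inferiority, with the mean difference in mL/min in brackets.

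| Excess loss | LOCF, losses without a value left out | Last value taken from the failed graft (5–15) | Loss scored 0 |
|---|---|---|---|
| 0 | 88 % (0.0) | 84 % (0.0) | 80 % (0.0) |
| 2 points | 85 % (−0.2) | 70 % (−0.8) | 61 % (−1.1) |
| 5 points | 78 % (−0.7) | 44 % (−2.3) | 33 % (−2.7) |

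The first row differs only through variance, so part of the gap lower down is added spread and not bias.

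**6. Spread when loss is scored 0.** With working-graft SD 20, mean 60 and a share q at 0, SD = √((1 − q) × 400 + q(1 − q) × 3600). This is 22.2 at q = 3 % and 25.2 at q = 8 %.

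**The case against.** **Silence is not a rule.** The article does not say that eGFR after graft loss is treated as missing, and such derivations often sit in the analysis plan. That has some force. But the article does state a rule for missing values in the primary test, and nothing in it takes lost grafts out of that rule. If the analysis plan does so, one sentence settles the point.

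**Early failures may have a value.** A reader might infer that everyone who fails before month 1 is dropped, or that the carried value always predates the loss. The article says neither. Visit 6 biochemistry or the day-5 creatinine used for slow graft function could supply a value, possibly from the failed graft. This objection stands, and I say only that exclusion is possible. However, visit 6 is triggered by stopping drug or withdrawing, not by graft loss, and the day-5 creatinine is not a visit in Table 4. How a loss is scored would then depend on timing.

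**The arm is not rewarded.** A reader might conclude that more graft loss helps an everolimus arm. It does not while the carried value lies below the arm mean; a gain would need selective removal of the worst kidneys. LOCF can also work against everolimus. If eGFR rises from 45 to 55 after month 1 and discontinuation is 8 points higher (both assumed), the bias is 0.08 × (45 − 55) = −0.8 mL/min.

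**Table 1 does not predict an excess.** One row reads "Death-censored graft survival was significantly lower with standard EVR vs. the high EVR arm at month 6" (90.2 % against 97.9 %). Both arms there are everolimus with cyclosporine, so it says nothing about everolimus against mycophenolic acid with tacrolimus. Trials in the same table with a mycophenolate control show composite failure of 11.5 % against 11.5 %, and 32.9 % and 26.9 % against 27.4 %.

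**An error rate would overreach.** The shift can be turned into a false non-inferiority rate: with SD 20 and 204 per arm, 1.5 to 2.5 mL/min gives 11.5 to 24.3 %. That treats 0 as the true value for a lost graft, which is a choice of estimand, and ignores the larger SD that scoring 0 brings. I do not rest the point on it.

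**Graft loss is not hidden.** It is reported in the key secondary composite and on its own. That limits the consequence to the primary test.

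**Conclusion.** The concern holds in limited form. Followed as written, the rule lets a lost graft contribute an eGFR from when it worked, and offers nothing for a dosed patient without a post-baseline creatinine. Should an everolimus arm lose more grafts, the primary test would under-penalise it.

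At a 5-point excess the masking would be a material part of the margin, roughly 13 to 54 % over the SDs considered; at 2 points it is modest. With no excess there is no shift in the mean difference.

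The SD, alpha, carried eGFR, working-graft mean and excess are all assumptions, and the margin is back-calculated. The documents give no graft-loss figures for these arms, so this is a weakness in the rule and not a prediction of the result.

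**What to change.** 1. State that no eGFR is carried forward or imputed across graft loss, and say how the primary analysis then treats these patients. Leaving them out removes their penalty entirely (step 3), so this change is not enough without item 2.
2. Pre-specify a key companion analysis of the primary comparison in the full analysis set. Score every graft loss as 0 mL/min, including early losses without a post-baseline value. Worst rank is an alternative, but it would need a margin on its own scale.
3. Call non-inferiority robust only if both analyses agree.
4. Handle death with a functioning graft separately and report it separately.
5. Say what happens to dosed patients who have no post-baseline eGFR for other reasons, and name one imputation method.

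The cost is wording, one derivation rule and one more analysis, settled before database lock; graft loss is already collected. The companion analysis has a larger SD, about 22 to 25 under the assumptions in step 6, and so less power. Power of the primary analysis is essentially unchanged. Scoring loss as 0 in the primary itself is defensible, but it is a debatable choice of estimand and would bring that loss of power into the main test.
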